### Interim analysis {21b}

When half of the intended study population has been reached, at 160 randomized participants, an interim analysis will be performed. The results of this analysis will determine if the study will be either continued or prematurely terminated, either due to futility or superiority. The difference in stone-free rates will be calculated alongside a 95% confidence interval (CI). The study will be terminated due to futility if the upper limit of this CI is below 5% or terminated due to superiority if the lower limit is above 15%. Interim analysis will be performed by the project leader. The results will be accessed and monitored by the data monitoring committee, after which the outcome (continuation or termination) of the trial will be concluded.

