## Oversight and monitoring

### Composition of the coordinating center and trial steering committee {5d}

The trial steering committee consists of the principal investigator and the project leader. The principal investigator and project leader meet on a weekly basis. The trial is evaluated by a trial steering committee consisting of both research team members and independent researchers in monthly research meetings. The protocol and statistical analysis plan were reviewed by an independent statistician, who is not a definite member of the trial steering committee.

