### Composition of data monitoring committee, its role, and reporting structure {21a}

The Data Monitoring Committee will monitor the safety and trial progress independently. The data monitoring committee consists of two trained independent data monitors. The data monitoring committee will perform independent data verification, check randomization procedures and confirm statistical analyses independently. It will report to the Medical Ethics Committee of our center and to the research team.

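### The project leader, who sits on the steering committee of this non-blinded trial, calculates the between-arm interim difference and will almost always know it while the second half is enrolled

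*Protocol article*

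**What the plan says.** The protocol article fixes the interim in section {21b}: "When half of the intended study population has been reached, at 160 randomized participants, an interim analysis will be performed". The analysis is comparative. It gives the difference in stone-free rates with a 95% confidence interval and stops the trial if the upper limit is below 5% (futility) or the lower limit is above 15% (superiority). The analyst is named: "Interim analysis will be performed by the project leader". The data monitoring committee then accesses the results, and continuation or termination is decided.

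Three other sections bear on this:

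- Section {5d}: "The trial steering committee consists of the principal investigator and the project leader", and "The principal investigator and project leader meet on a weekly basis". The same section adds that a steering committee that includes independent researchers evaluates the trial monthly. It also says that the protocol and analysis plan were "reviewed by an independent statistician, who is not a definite member of the trial steering committee".
- Section {21a}: the data monitoring committee has two independent monitors who, among other tasks, "confirm statistical analyses independently". The committee reports to the ethics committee and to the research team.
- Sections {8} and {17a}: the trial is non-blinded.

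Nothing in the article masks the arm labels at the interim, withholds the result from the trial team or pauses recruitment.

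**The concern.** An interim estimate by arm is normally kept from those who run a trial, because knowing it can change how the rest of the trial is conducted. Here the article gives the calculation to one of the two named steering committee members, although it describes independent people who could do it.

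The surgeon knows the allocation, so several later decisions could respond to a known trend and differ by arm. They include how hard fragments seen on the CBCT scan are pursued, whether and when to re-intervene, and how stone-related events are handled. Decisions on trial conduct, such as a protocol amendment, are exposed as well. Once the team has seen the comparison, this cannot be undone, so the matter has to be settled before the interim.

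**Working it through.** **Step 1. The plan's own figure.** Inputs from section {14}: 60% versus 75%, power 80%, alpha 0.05 (taken as two-sided). With pooled variance and no continuity correction:

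n = [1.960 × √(2 × 0.675 × 0.325) + 0.842 × √(0.60 × 0.40 + 0.75 × 0.25)]² / 0.15² = (1.298 + 0.550)² / 0.0225 ≈ 152 per arm.

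The total is 304, and 304 / 0.95 = 320. The stated sizes reproduce, and the interim at 160 means about 80 per arm.

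**Step 2. What stopping would need.** Assume 80 per arm, all with a 4-week CT, and a Wald interval. At 60% and 75% the half-width is

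1.96 × √(0.60 × 0.40/80 + 0.75 × 0.25/80) = 1.96 × √0.00534 = 0.143.

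- Superiority needs an observed difference above about 0.15 + 0.143 = 0.293.
- Futility needs an observed difference below about 0.05 − 0.143 = −0.093.

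**Step 3. How often the trial continues.** Exact enumeration of the two binomial counts under the same assumptions, with 60% in the control arm:

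| True difference (points) | P(stop, futility) | P(stop, superiority) | P(continue) |
|---|---|---|---|
| 0 | 0.0937 | 0.0001 | 0.906 |
| 5 | 0.0260 | 0.0007 | 0.973 |
| 10 | 0.0047 | 0.0051 | 0.990 |
| 15 | 0.0005 | 0.0284 | 0.971 |
| 20 | 0.00003 | 0.1154 | 0.885 |

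**Step 4. How long the knowledge lasts.** At the 60–70 inclusions per year in section {14}, 160 patients take 160/70 = 2.3 to 160/60 = 2.7 years. If recruitment runs on during the 4-week wait for the last CT, about 60 × 4/52 = 4.6 to 70 × 4/52 = 5.4 more patients are enrolled first, so about 155 remain.

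**Step 5. What the project leader learns beyond a bare decision.** A message to continue shows only that the observed difference lies roughly between −9 and +29 points, a range of about 38 points. The project leader holds the estimate itself and its interval.

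**Step 6. What the existing safeguards cover.**

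| Safeguard | Protects | Leaves open |
|---|---|---|
| Independent radiologist unaware of allocation (Primary outcome measure) | Reading of the 4-week CT | How much stone was left to be read |
| Concealed sequence, varying blocks ({16a}–{16c}) | Who gets which arm | Conduct once the arm is known |
| Committee access and confirmation ({21b}, {21a}) | Correctness of the interim and the stopping decision | Who has already seen the result |

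**The case against.** The strongest reply has four parts.

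- **The link to conduct is inferred.** A reader might conclude that the estimate goes straight to the people who choose cases and finish operations. The article does not support that. It does not say that the project leader operates, judges who can be randomised or tells surgeons the result. The urologist decides when surgery is done, and a trained nurse randomises. The documented link is the weekly meeting with the principal investigator, whom the article does not identify as an operator. This stands, so the influence may be only indirect.
- **Changes before randomisation do not unbalance the arms.** A reader might infer that knowing the trend biases the comparison through selection, or through the search made before randomisation. Allocation is concealed and comes afterwards, so such changes fall on both arms. They can shift case-mix and the applicability of the result, and procedures that are not randomised are recorded. It is also tempting to read a large discretionary share from section {14}, but its two ranges (60–70 inclusions, 80–100 procedures) allow anything from 1 − 70/80 = 12.5% to 1 − 60/100 = 40% not included. Part of that is safety terminations. No figure for selection can be drawn from it.
- **Open-label influence exists anyway.** The Discussion already concedes that the unblinded urologist may affect secondary outcomes, and in a single centre the 4-week results are seen at routine visits. This stands in part: the fix will not hide every impression of the trend. An impression is still much weaker than a calculated difference with its interval. The Discussion regards the primary outcome as safe, but a blinded reader records what was left behind, and effort after allocation can change that.
- **The full protocol or analysis plan may restrict access.** It may. The article nevertheless states who performs the comparison, and that is a rule, not an omitted detail. The data monitoring committee's confirmation and the independent researchers at the monthly meetings are real oversight, but neither keeps the result from the project leader.

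**Conclusion.** The point holds as a weakness in a stated rule. A steering committee member of a non-blinded trial will calculate the between-arm difference and, with probability about 0.97 at 60% versus 75% and 0.91 at no difference (0.885 to 0.990 over true differences of 0 to 20 points), will know it while most of the remaining patients, about 160 at most, are enrolled. These figures assume 80 per arm, complete CT data, a Wald interval and 60% in the control arm. They measure how likely it is that the knowledge persists into the second half, not the size of any bias, which the documents do not allow one to estimate.

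The exposure that can differ by arm is surgical effort after allocation, re-intervention decisions and other secondary outcomes. Trial-conduct decisions are also at risk. Effects before randomisation would bear on case-mix and applicability only. The sample size and the final test are not affected.

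**What to change.** Make both changes before the interim:

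1. **Section {21b}:** the data monitoring committee, or the independent statistician who reviewed the plan if available, receives the data and runs the comparative interim. Only the committee sees the results. The project leader and principal investigator are told only to continue or to stop.
2. **Section {21a}:** while the trial continues, the committee's report to the research team carries the same restriction. Changing {21b} alone would leave this route open.

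The cost is a short amendment that needs ethics committee approval, and a small amount of work for an independent person. The article says only that the statistician reviewed the plan, so willingness to run the interim has to be confirmed. Sample size, stopping boundaries and patient care do not change.

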### Methods for additional analyses (e.g., subgroup analyses) {20b}

In order to assess the ideal PCNL characteristics for performing a CBCT-guided PCNL, subgroup analyses will be performed in order to assess the primary and secondary outcome measures for different stratification variables. These stratification variables include the surgery characteristics, stone size, stone type and stone location.

### Methods in analysis to handle protocol non-adherence and any statistical methods to handle missing data {20c}

Analysis will be by intention-to-treat. We have no intention of imputing missing values. We will assess for patterns in possible missing data but expect any missing data to be missing at random, since the follow-up protocols are identical for both study arms.

### Plans to give access to the full protocol, participant level-data and statistical code {31c}

The full protocol, trial data and statistical code may be accessed upon request by contacting the corresponding author.

## Oversight and monitoring

### Composition of the coordinating center and trial steering committee {5d}

The trial steering committee consists of the principal investigator and the project leader. The principal investigator and project leader meet on a weekly basis. The trial is evaluated by a trial steering committee consisting of both research team members and independent researchers in monthly research meetings. The protocol and statistical analysis plan were reviewed by an independent statistician, who is not a definite member of the trial steering committee.

### Composition of data monitoring committee, its role, and reporting structure {21a}

The Data Monitoring Committee will monitor the safety and trial progress independently. The data monitoring committee consists of two trained independent data monitors. The data monitoring committee will perform independent data verification, check randomization procedures and confirm statistical analyses independently. It will report to the Medical Ethics Committee of our center and to the research team.

### Adverse event reporting and harms {22}

The main risks for participants consist of an added radiation exposure and added surgery time if allocated to the interventional group. The added radiation exposure that is expected is calculated to be 1.5–2.0 mSv per CBCT scan. This effective dose corresponds to a minor to intermediate risk category IIb, where the benefit for the participant is aimed at cure or prevention of disease according to the ICRP publication 6 2[17]. Surgery time needed for preparation, performing, and interpreting an intraoperative CBCT scan is around 8 minutes, according to our recently conducted pilot study. If imaged RFs are extracted, the median total extra surgery time needed in that pilot study was 20 min. This added time increases the anesthesia duration and could thereby increase the risk of perioperative complications.

Adverse events (AEs) that may occur can be a result of the risks mentioned above. All AEs will be registered in the REDCap database. Assessment of AEs will be performed and any serious AEs (SAEs) will be reported. The sponsor will report SAEs through the web portal “ToetsingOnline” to the accredited Medical Ethical Committee that approved the protocol, within 7 days of first knowledge for SAEs that result in death or are life-threatening followed by a period of a maximum of 8 days to complete the initial preliminary report. All other SAEs will be reported within a period of maximum 15 days after the sponsor has first knowledge of the SAEs.

### Frequency and plans for auditing trial conduct {23}

This study has been approved by the local Medical Ethics Committee as a low-risk study (Risk Classification 1). The database will be monitored once yearly according to standard ethical practice for a low-risk study clinical trial in our center. Monitoring is performed by a trained monitor from our center who is independent. Plans for communicating important protocol amendments to relevant parties (e.g., trial participants, ethical committees) {25} of our department. The Medical Ethics Committee will receive a yearly update of the status of the trial. Any protocol amendments will be submitted to the Medical Ethics Committee for approval.

### Protocol amendments

No relevant protocol amendments have been implemented yet.

### Ancillary and post-trial care

The care that participants receive does not differ from standard care apart from the randomization with a possible intervention and data collection. No specific measures are undertaken for ancillary or post-trial care.

### Dissemination plans {31a}

We plan to release the study results to referring physicians, participants, future patients, and the general medical community. We seek to reduce the interval between completion of data collection and dissemination of study results to a minimum.

## Discussion

This study will be the first randomized trial evaluating the use of CBCT during PCNL. With a design that standardizes and equalizes circumstances for both arms except for the intervention that is to be evaluated, the imposed burden for participants is kept low while maintaining a high level of evidence.

To date, it is unclear whether the use of CBCT during PCNL can genuinely increase stone-free rates and decrease stone-related morbidity. A positive result of the proposed trial could lead to the adaptation of hybrid operating rooms for PCNL on a larger scale. The results will aid in indicating the circumstances in which performing a “hybrid PCNL” will result in a greater chance of a positive outcome.

Several limitations should be noted for this study. First of all, the unblinded urologist performing the procedure could affect the postoperative outcomes, thereby possibly influencing the secondary outcome measures for this trial. The primary outcome, however, the stone-free status on a 4-week postoperative CT scan, is an objective outcome measure that cannot be influenced in this way.

An ethical dilemma that arises with regard to the design of this study, is that with a relatively large sample size and a 1:1 randomization allocation ratio, a substantial number of participants could be deprived of a potentially superior treatment. Considering possible downsides, e.g., high costs, additional procedure duration, and radiation exposure, a study with a high level of evidence is required in order to conclude whether this technique should be either implemented or rejected.

The interim analysis imposes a limitation for this study, since analyzing the data multiple times increases the chance of occurrence of a Type I error. In this study, no alpha adjustments are made besides setting broad termination boundaries including 95% confidence intervals. This was done in order to maintain a reasonable chance of detecting superiority while maintaining a commonly used alpha of 0.05 at the final analysis.

Another limitation concerns the long duration of the trial caused by a large sample size in a single-center setting. Since PCNL methods, CBCT scanners, and follow-up protocols may vary widely per center, analysis of data from multiple centers would become a challenge. Along with this, not many centers have a dedicated urological hybrid operating room at their disposal that allows for performing a hybrid PCNL in every case, which is required for this study design. In this trial, we expect a high rate of participation and a low rate of exclusion, resulting in a database of nearly every PCNL performed in our center. Therefore, this trial provides a basis of data for a follow-up period of many years to come, since we expect most participants to consent to longitudinal data collection. On that account, we consider this trial to be a valuable investment that is likely to result in a broad range of future research opportunities in the field of kidney stone surgery.

## Trial status

The first participant was recruited in January 2020 and the trial is currently open to recruitment. The current protocol version is version 4, 16 March 2021. Recruitment is expected to complete in 2026.

## Abbreviations

AE: Adverse event
CBCT: Cone beam computed tomography
CT: Computed tomography
GCP: Good Clinical Practice
GDPR: General Data Protection Regulation
HU: Hounsfield Units
NTR: Netherlands Trial Register
PCNL: Percutaneous nephrolithotomy
RCT: Randomized controlled trial
REDCap: Research Electronic Data Capture
RF: Residual fragment
SAE: Serious adverse event
SPSS: Statistical Package for the Social Sciences
SRE: Stone-related event
UMCG: University Medical Center Groningen
